## **7.Study Hypothesis**

(1) The experimental group will be superior to the control group in terms of VAS-P reduction and IAP control,

suggesting that intermittent epidural injections provide superior pain management and visceral protection.

(2) The incidence of adverse events in the experimental group will not be higher than that in the control group, and the length of hospitalization in the ICU and 28-day mortality will be lower, suggesting that the intermittent injection method is safe and may improve prognosis.

(3) Analgesic satisfaction scores will be higher in the experimental group than in the control group, suggesting that the nurse-led pain management program is more responsive to patient needs.

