## 12. Sample size

This study is a randomized controlled trial, and the primary outcome indicator is the VAS-P score. From the literature review, it is known that the mean VAS-P scores after the intervention of similar control group protocols are 1-3, and there is no study similar to the experimental group, and the mean VAS-P scores of the pre-experimental group are 1-2. It is proposed to formulate the standard deviation of the two groups combined  $\sigma = 2.5$ , and it is expected that the pain symptom scores of the experimental group can be decreased by  $\delta = 2$ . Setting a bilaterality of  $\alpha = 0.05$ , the degree of certainty is 90%, and based on the formula of the sample size [Formula 1](#), the sample size is calculated for each group of  $N = 33$  participants. Assuming a 15% dropout rate, a total of 76 participants were needed based on a 1:1 randomization ratio.

*Formula 1:*

$$n = \frac{2(z_{\alpha} + z_{\beta})^2 + \sigma^2}{\delta^2}$$

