### **16.Data collection process**

After patients were admitted to the ICU, eligible study subjects were screened according to the inclusion and exclusion criteria. Before enrollment, the following baseline data were collected: patients' general information: including age, gender, and time of admission; important clinical and diagnostic information: including etiology of onset, time from onset to admission, time from onset to admission to the ICU, time from onset to TEA, history of previous chronic diseases, related complications, type of SAP pathology, CTSI score, Ranson score, APACHE-II score and major interventions during hospitalization; and pain score and intra-abdominal pressure before epidural placement. These baseline data cover the basic characteristics, clinical status and pain of the patients and provide a comprehensive reference for subsequent assessment of pain management outcomes.

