## **19.Primary outcome measure**

Visual Assessment Scale-Pain (VAS-P): which consists of a 100-mm straight line, with one end indicating “no pain at all” and the other end indicating “the most severe pain imaginable”, with the patient marking the corresponding position on the line to represent his/her pain level. Patients marked the corresponding position on the line to represent their pain level. The data were collected by the data collectors at the specified time points (0h, 1h, 6h, 12h, 24h, 48h, 72h). Among them, 0h was before epidural placement, and the other times were 1h, 6h, 12h, 24h, 48h and 72h after epidural placement.

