## **21.Adverse Events**

Puncture-related AE : Healthcare workers observe and record the following 8 indicators during daily care and examination: spinal cord and nerve root injury, epidural hematoma, puncture site infection, total spinal anesthesia, headache after dural puncture, intradural infection, catheter blockage, catheter breakage and ectasia. The number of cases of AE was counted for the period of epidural placement.

Drug-related AE: Pain management nurses observed and recorded the following 8 indicators after the patient's medication: anaphylaxis, hypotension, nausea/vomiting, itching, tremor, sensory disturbances in the lower limbs, fever, decreased oxygen saturation, bradycardia or tachycardia. The statistical methods and times were the same as those for puncture-related AE.

22.Outcome Indicators

Puncture surgery rate (PSR): Calculate the ratio of the number of successful puncture cases to the total number of punctures, which was counted by the data collector.

Length of stay in ICU (ICU-LOS): when patients are transferred out of ICU, the total number of days of ICU stay is recorded.

28-day mortality rate (28D-MR): count the number of patients who died within 28 days and calculate the 28-day mortality rate.

Satisfaction with analgesic effect (SAE): patients' satisfaction with the analgesic effect was assessed using a 0-10 scale, with 0 indicating very dissatisfied and 10 indicating very satisfied. It was collected by the data collector on the day of epidural tube removal.The intervention and data collection process are shown in [Figure 4](#).

[figure not shown]

Figure 5: Intervention and Data Collection Process

23. Quality control

(1) All staff must undergo standardized training and pass assessments to ensure consistent implementation of the intervention, minimizing both executor and assessor bias.

(2) Collected data will be cross-verified by two researchers before being entered into the system to ensure data accuracy.

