| Length of stay in ICU (ICU-LOS)                  |                 |            |                 |                |                |                |                |                |                |                |                | X              | X              |           |
| 28-day mortality rate (28D-MR)                   |                 |            |                 |                |                |                |                |                |                |                |                | X              | X              |           |
| Satisfaction score with analgesic effect (SAE)   |                 |            |                 |                |                |                |                |                |                | X              |                |                |                |           |

tx: Remove the thoracic epidural catheter

ty and tz: transfer out of the ICU or be admitted to the ICU for 28 days.

Figure 5:SPiRiT-Figure:Schedule of enrolment, interventions and assessments

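### ICU stay counts days before randomisation, and 28-day mortality has no stated origin, with the schedule footnote pointing to ICU admission; both clocks should start at randomisation

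*Protocol*

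**What the plan says.** - **ICU stay.** Section 22 (Outcome Indicators) fixes the measure: "when patients are transferred out of ICU, the total number of days of ICU stay is recorded". It names no start other than the ICU stay itself.
- **28-day mortality.** The same section says only: "count the number of patients who died within 28 days and calculate the 28-day mortality rate". It does not say from when.
- **Schedule.** In section 35 (SPIRIT-Figure) both outcomes are marked at t_y and t_z, which the footnote explains as "transfer out of the ICU or be admitted to the ICU for 28 days".
- **Enrolment.** Section 16: "After patients were admitted to the ICU, eligible study subjects were screened according to the inclusion and exclusion criteria". Section 11 also recruits in the ICU, and section 9 puts randomisation before catheter placement. The inclusion and exclusion criteria set no maximum number of ICU days before enrolment.
- **Other clocks.** Section 19 starts the pain scores elsewhere: "0h was before epidural placement, and the other times were 1h, 6h, 12h, 24h, 48h and 72h after epidural placement".
- **Baseline data.** Section 16 lists "time from onset to admission to the ICU, time from onset to TEA" but no randomisation date.
- **Use.** Hypothesis 2 in section 7 predicts, for the experimental group, that "the length of hospitalization in the ICU and 28-day mortality will be lower". Section 24 compares ICU stay by t-test or Mann-Whitney test, with no adjustment stated, and section 13 describes no stratification.

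**The concern.** An outcome meant to show an effect of allocation should begin at allocation. Here the ICU-stay clock begins at ICU admission, and the mortality clock appears to do so as well. Call the ICU days before randomisation the lag. Neither epidural regimen can change it.

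The lag enters the two outcomes in different ways. In ICU stay it is added to every patient's total, so its spread becomes noise around any treatment effect. In mortality, if the 28 days run from ICU admission, it is time that every enrolled patient has by definition survived. It uses up part of the window, and patients randomised late are observed for less time after allocation than those randomised early.

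At stake is the precision of two results named in Hypothesis 2, in a trial of 76 patients. Shorter ICU stay is also part of the practical case made in sections 28 and 30.

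**Working it through.** **Inputs from the protocol.** The total of 76 patients at 1:1 gives 38 per arm (section 12). That total reproduces: 2 × (1.960 + 1.282)² × 2.5² / 2² = 32.8, so 33 per group, and 33 × 1.15 = 37.95, so 38 per group and 76 in all. It was set for the pain score. The protocol gives no planning figure for ICU stay or mortality, so there is none to reproduce for these outcomes.

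**Inputs assumed.** The documents do not give the length or spread of the lag, the SD of ICU stay after treatment starts, or a 28-day risk. All are assumed below and shown over a range. The short interval between randomisation and catheter placement is ignored.

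**1. ICU stay: variance.** Total stay = lag + later stay. With lag SD *l* and later SD *s*, independent, the variance ratio is (s² + l²) / s². With s = 7 days:

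| Lag SD *l* (days) | (49 + l²) / 49 | Rise in variance | 1.96 × l × √(2/38) (days) |
|---|---|---|---|
| 2 | 53 / 49 = 1.08 | 8% | 0.90 |
| 3 | 58 / 49 = 1.18 | 18% | 1.35 |
| 5 | 74 / 49 = 1.51 | 51% | 2.25 |

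The last column is the 95% range (±) of the chance difference in mean lag between arms. It is the same extra variance expressed in days, not a second harm.

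Independence matters. With correlation ρ the variance is s² + l² + 2ρsl. A positive ρ makes the rise larger. A negative ρ makes it smaller, and below −l/(2s) (−0.14, −0.21 and −0.36 for the three rows) total stay would be less variable than later stay.

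**2. ICU stay: power.** A second set of assumptions: s = 8 days, a true difference of 5 days, 38 per arm, two-sided 5%. Power ≈ Φ(5 / (SD × √(2/38)) − 1.96).
- No lag in the outcome: SD 8, power 77.8%.
- Lag SD 1, 2 or 4 days: SD 8.06, 8.25 or 8.94, power 77.1%, 75.3% or 68.3%.

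The loss is small for a tight lag and material only for a wide one.

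**3. Mortality window, if day 28 is counted from ICU admission.** Window after randomisation = 28 − lag:

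| Lag (days) | Window (days) | Shorter by | Counted risk if true 28-day risk is 30% | If 10% |
|---|---|---|---|---|
| 1 | 27 | 3.6% | 29.1% | 9.7% |
| 3 | 25 | 10.7% | 27.3% | 9.0% |
| 5 | 23 | 17.9% | 25.4% | 8.3% |
| 7 | 21 | 25.0% | 23.5% | 7.6% |

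The risks use a constant hazard: counted risk = 1 − (1 − p)^((28 − lag)/28). A given lag acts in the same way in either arm.

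**The case against.** **Is there bias?** A reader might infer that pre-treatment days bias the comparison, or that a shorter stay in one arm could be explained away by earlier enrolment. The design does not support that. The lag is fixed before allocation, so randomisation balances it in expectation. Surviving to enrolment is required equally in both arms and creates no immortal time between them. Chance imbalance in lag is already inside the standard error of the planned tests, which keep their error rate. This part of the objection stands in full.

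**Is mortality defined from ICU admission?** A reader might also infer that it is. Section 22 gives no origin, and the footnote explains two schedule columns shared by two outcomes; it is not an endpoint definition. The exact statement is that the origin is left open and the only indication points to ICU admission. An open origin alone could be settled in a statistical analysis plan that is not shown. However, the schedule wording points to an unsuitable origin, and the ICU-stay definition is explicit.

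**Is total stay a legitimate measure?** Yes, as a measure of resource use, and the protocol does mention cost. That supports reporting it. It does not make it the better measure of what allocation changed.

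**Are the sizes real?** They rest on assumed SDs. The 51% needs the widest lag considered, and nothing in the protocol shows that lags are long or variable.

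**Is it already handled?** In part. The lag to catheter placement can be derived from the two onset times in section 16, so an imbalance would be visible. No use of it in the analysis is stated.

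**Conclusion.** The point holds as a matter of precision and comparable follow-up, not of bias. ICU stay as written includes days that no arm can affect. 28-day mortality has no stated origin, and on the reading that the schedule suggests, the window after randomisation shortens day for day with the lag.

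Under an assumed lag SD of 2, 3 or 5 days and an assumed, independent later-stay SD of 7 days, the variance of ICU stay rises by about 8%, 18% or 51%. If lags are short and uniform, the effect is close to nil. Both outcomes are non-primary. The pain endpoint, its clock and the sample size are untouched. The change is worth making because it is cheap and replaces a noisier definition with the standard one.

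**What to change.** - In section 22, define ICU stay as days from randomisation to ICU discharge, and 28-day mortality as death within 28 days of randomisation.
- In section 35, redefine t_y as transfer out of the ICU and t_z as day 28 after randomisation.
- In section 16, add the date and time of randomisation, and keep ICU days before randomisation as a baseline variable.
- Total ICU stay may still be reported descriptively as the resource measure.

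**Cost.** Two definitions, one footnote and one date that allocation already generates. For patients randomised late, vital status is read a few days later than the footnote now implies. Sample size and treatment do not change.

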## **I. Research Background and Current Status**

Acute pancreatitis (AP) is one of the common acute abdominal conditions in clinical practice, which may be associated with the failure of one or multiple organ functions. In high-income countries, the annual incidence rate is 34 cases per 100,000 person-years. The incidence of AP is on the rise worldwide, imposing a significant burden on healthcare and society. According to the revised Atlanta Classification of Pancreatitis in 2012, AP is categorized into three grades: mild acute pancreatitis (MAP), moderate severe acute pancreatitis (MSAP), and severe acute pancreatitis (SAP). These three types of pancreatitis have different clinical courses and outcomes. Most patients with MAP recover within one week, while those with SAP and MSAP have a more rapid disease progression, often accompanied by necrosis of peripancreatic tissues or (and) organ failure. The treatment is challenging, and the mortality rate is as high as 30%. Despite improvements in treatment and intensive care, SAP remains associated with high mortality. Therefore, early de-escalation of severity in SAP is crucial for reducing complications and improving prognosis.

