##### **Exclusion criteria**

- (1) Spinal deformity, inappropriate for epidural puncture, failure of thoracic epidural puncture.
- (2) Patients with chronic SAP, patients with SAP combined with pregnancy, patients with pancreatic pseudocyst and infection.
- (3) Patients with contraindications to epidural analgesia, such as coagulation disorders, local infection, allergy to lidocaine, etc.
- (4) Combined with severe cardiac, pulmonary, hepatic and renal failure, serious infection, malignant diseases and autoimmune diseases.
- (5) Patients with incomplete medical records.

Dropout criteria

- (1) The duration of epidural placement is less than 3 days.
- (2) The patient withdraws informed consent for any reason during the study.
- (3) Unable to continue to complete the study for other reasons, such as a change in condition requiring transfer to or discharge from the hospital or refusal of further treatment or evaluation.

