#### **24.Data analysis**

Data will be analyzed in this study using GraphPad Prism software to ensure accuracy and consistency of results. For baseline characteristics data, patients' age, gender, admission time, and disease-related clinical information will be descriptive statistics, Categorical variables will be presented as frequencies and proportions, whereas normally distributed continuous variables will be described using means and standard deviations. For non-normally distributed data, descriptive statistics will utilize median and percentile values (P25 and P75). Between-group comparisons will be carried out using t-tests, analysis of variance, chi-square tests, Mann-Whitney U tests, and statistical methods for repeated measures data to assess differences among the groups. The significance level in this study will be set at  $\alpha=0.05$ , with  $P<0.05$  indicating statistical significance.

The changes in the primary outcome indicator VAS-P at different time points (0h, 1h, 6h, 12h, 24h, 48h, 72h) will be assessed by repeated measures analysis of variance (ANOVA) if the data conform to a normal distribution. Secondary outcome indicators, such as intra-abdominal pressure (IAP), will be analyzed in the same manner. The number of additional interventions (NAI) and the dose of coadministered medication (DCD) will be expressed as mean  $\pm$  SD or median (IQR), and comparisons between groups will be made using the t-test or the Mann-Whitney test. The number of days of epidural placement (NDEP) will also be subjected to descriptive statistics and between-group comparisons. The number of cases of adverse events (AE) will be expressed as frequency, and comparisons between groups will be made using the chi-square test or Fisher's exact test. The outcome indicators, including puncture success rate (PSR), length of stay in the ICU (ICU-LOS), 28-day mortality rate (28D-MR), and satisfaction with analgesic effect score (SAE), will be subjected to descriptive statistics and between-group comparisons using the chi-square test or Fisher's exact test, as well as the t-test or the Mann-Whitney test.

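### ICU length of stay is compared with no rule for deaths in the ICU, so deaths are either dropped or read as short stays; separately, the schedule leaves day-28 vital status after ICU transfer unclear

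*Protocol*

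**What the plan says.** Section 22 of the protocol defines ICU length of stay (ICU-LOS) as follows: "when patients are transferred out of ICU, the total number of days of ICU stay is recorded". It defines 28-day mortality (28D-MR) as: "count the number of patients who died within 28 days and calculate the 28-day mortality rate". Neither definition names the day from which the count starts.

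Section 24 assigns chi-square or Fisher tests to the categorical outcome indicators, "as well as the t-test or the Mann-Whitney test" for the others. ICU-LOS falls in the latter group.

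Hypothesis 2 in Section 7 predicts for the experimental arm that "the length of hospitalization in the ICU and 28-day mortality will be lower", and takes this as a sign that the method may improve prognosis.

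The schedule in Section 35 marks both ICU-LOS and 28D-MR in columns ty and tz. One footnote defines the two columns together: "transfer out of the ICU or be admitted to the ICU for 28 days".

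Two of the dropout criteria in Section 11 also matter here: "The duration of epidural placement is less than 3 days", and inability to continue for reasons such as "a change in condition requiring transfer to or discharge from the hospital".

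**The concern.** Death in the ICU ends the stay without a transfer out. The protocol fixes the definition, the tests and a directional hypothesis for ICU-LOS, but not how such a patient is handled. Two readings are open.

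- **No value.** The comparison is then among patients who survived the ICU, a group formed after randomisation and possibly different between arms.
- **Days to death as the value.** An early death then becomes a short stay, which Hypothesis 2 counts as a good result.

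The missing-data rules in Section 24 do not settle it. They average neighbouring time points, exclude patients with two consecutive gaps, or choose an imputation method case by case. ICU days after death are not missing values to be filled in. The dropout criterion on catheter duration could also remove an early death from the data altogether.

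At stake is the reading of Hypothesis 2. As defined, its two parts can pull against each other, because an arm that saves lives can show a longer mean stay.

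**Working it through.** **1. The plan's own figure.** The protocol computes nothing for ICU-LOS or mortality. Its only calculation is the VAS-P sample size (Section 12: SD 2.5, difference 2, two-sided 0.05, 90% power). In the standard product form, 2 × (1.960 + 1.282)² × 2.5² / 2² = 32.8, so 33 per group. Then 33 × 1.15 = 37.95, so 38 per group and 76 in total, as stated. The 38 per arm is used below.

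**2. Patients who could be affected.** Section I says of the more severe forms that "the mortality rate is as high as 30" per cent.
- At 30%: 0.30 × 38 = 11.4, about 11 per arm.
- At an assumed 10%: 0.10 × 38 = 3.8, about 4 per arm.

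The first number is a ceiling (see the objection).

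**3. Deaths counted as short stays, by hand.** Assumed, not in the documents: survivors stay S = 14 days and deaths occur on day D = 5. With mortality p, mean stay = (1 − p) × S + p × D.
- p = 20%: 0.8 × 14 + 0.2 × 5 = 12.2 days.
- p = 30%: 0.7 × 14 + 0.3 × 5 = 11.3 days.

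The arm with 10 points more deaths looks 0.9 days better. In general the shift is the mortality difference times (S − D), here 0.10 × 9 = 0.9. It is zero when mortality is equal.

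**4. Simulation.** Assumed: 38 per arm; survivors' stay log-normal with median 12 days and log-SD 0.6, the same in both arms; ICU deaths uniform over days 3 to 10; 3,000 runs; Mann-Whitney at 0.05.

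| Mortality, control / experimental | Deaths as short stays: shift in mean (experimental − control) | Rejects | Deaths dropped: rejects | Death ranked worst: rejects |
|---|---|---|---|---|
| 20% / 10% | +0.7 days | 7% | 5% | 12% |
| 30% / 15% | +1.2 days | 12% | 5% | 21% |
| 30% / 10% | +1.6 days | 17% | 5% | 33% |

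The formula in step 3 agrees. Mean survivor stay is 12 × exp(0.6²/2) = 14.4 days and mean time to death is 6.5 days. The expected shifts are therefore 0.10, 0.15 and 0.20 times 7.9, or 0.8, 1.2 and 1.6 days.

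Counting deaths as short stays makes the arm with fewer deaths look longer in the ICU. Ranking death worst reverses the direction. Dropping deaths shows no shift only because this model makes death unrelated to the stay a patient would otherwise have had. With equal mortality (10% or 30% in both arms), rejection stays at about 4 to 5% under every rule.

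**5. The same hand example under ICU-free days.** If the 14 days count from randomisation, a survivor scores 28 − 14 = 14 and a death scores 0. The mean is 0.8 × 14 = 11.2 at 20% mortality and 0.7 × 14 = 9.8 at 30%. The arm with fewer deaths is now ahead by 1.4 days.

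**6. The schedule footnote for 28D-MR.** Two readings fit.
- ty is ICU transfer and tz is day 28 for everyone: deaths after transfer are captured.
- A patient reaches one event or the other: assessment ends at transfer for those who leave early, and later deaths up to day 28 are missed.

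The documents give no figure from which to compute how many would be missed.

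**The case against.** Several points on the other side stand.

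- **The mortality schedule.** A reader might infer that 28-day mortality is assessed only at ICU transfer, so that later deaths are lost. The documents do not say this. Section 22 counts deaths within 28 days without restricting them to the ICU, and the schedule marks 28D-MR in both columns. It also marks clinical status at tz but not at ty, which suggests that tz is a separate time. Section 29 promises patient follow-up during and after the study. What remains is that the footnote is ambiguous and no day-28 contact is described.
- **The time origin.** A reader might also infer that the 28 days run from ICU admission. Only the footnote points that way, and Section 22 names no origin. It needs stating because patients are screened and enrolled after ICU admission (Sections 11 and 16).
- **A false claim of benefit.** Mortality is tested in its own right, so an arm with shorter stays because more patients died would also show higher mortality, against Hypothesis 2. If the experimental arm has fewer deaths, counting deaths as short stays works against it. The defect muddles the hypothesis; it does not simply favour it.
- **Size.** The stays in the examples are assumed. The 30% is an upper background figure covering moderately severe as well as severe disease, while this trial takes awake patients aged 18 to 65 and excludes severe organ failure and serious infection. It also treats every death as an ICU death.
- **Detail left to the SAP.** Handling of deaths in a length-of-stay variable often is. Here, though, the protocol already fixes the recording event, the tests and the predicted direction, and together they leave only the two unsatisfactory readings. The 28-day column gives a recording time for ICU-LOS, but still no rule for a patient who has died.

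**Conclusion.** The ICU-LOS point holds. Following the protocol as written either restricts the comparison to survivors or credits early death as a short stay. Under the second reading the bias favours the arm with more early deaths, by 0.7 to 1.6 days across the assumed scenarios with mortality differences of 10 to 20 points. With equal mortality there is little distortion. The patients concerned number at most about 11 of 38 per arm, and about 4 of 38 at an assumed 10% mortality.

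For 28-day mortality the finding is narrower: an ambiguous footnote and an unstated time origin, not a demonstrated loss of deaths.

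The issue touches Hypothesis 2 and leaves the primary VAS-P analysis and the sample size alone. Severity is minor to moderate because these are non-primary outcomes. Confidence is moderate: the gap is plain in the text, but its size rests on assumed stays and mortality.

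**What to change.** 1. In Sections 22 and 24, make the between-arm comparison one of ICU-free days from randomisation to day 28, with death by day 28 scored 0, tested by Mann-Whitney. Keep ICU-LOS as description, reported by survival status.
2. Show 28-day mortality beside ICU-free days. The new measure is a composite of death and stay, and a difference in it cannot be read without knowing which part drives it. That is its main drawback.
3. In Section 22, state that 28-day mortality runs from randomisation. In Section 35, define ty and tz separately, with a day-28 vital status mark for every randomised patient, including those transferred, discharged or classed as dropouts under Section 11.

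The cost is two reworded definitions, one schedule change, and a record check or call at day 28 for patients who have left the ICU, which the follow-up mechanism in Section 29 can carry. The Mann-Whitney test is already planned, and the sample size does not change.
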